### Sample size

The study sample size is estimated as 8000 women from eight GP practices. This is a pragmatic sample size based on the number of eligible women (between the ages of 50 and 70) at eight average sized GP practices. This sample size will allow for the reliable estimation of key feasibility figures and detection of signal of efficacy for the future full trial.^20^

### Data collection and statistical analysis

The feasibility outcomes, including recruitment figures, fidelity of intervention and outcome measure completion rates, will be reported and checked against the prespecified progression criteria. We will assess the screening uptake rates and report results by key characteristics (eg, ethnicity, area deprivation). The intraclass coefficient calculated from this data and effect size of intended outcomes will be used to inform the sample size (power calculation) for the definitive RCT. Participant data from the eight included GP practices collected by the HEY BSS will be linked to data held by NHS England (through the DARS process and following receiving Section 251 approval from Confidentiality Advisory Group (CAG) on deprivation scores for the residential locations and ethnicity data. Women who have opted out from the study or through the national opt-out will be removed from the data prior to it being sent to NHS England. Following linkage, NHS England will remove all patient identifiers and transfer the pseudonymised data to the University of Hull Data Safe Haven for analysis. The attendance data collected from HEY BSS for the study participants will be linked to this data set.

Data will be collected by the transport providers on trips taken to the breast screening appointments. Transport providers will be required to invoice for the cost of these journeys and will document the number of trips and duration (time) including waiting time between being dropped off for the appointment and being collected for the return journey. This cost per trip is an integral part of the costs that will be used in the cost-effectiveness analysis.

All participants, in both the control and intervention arms, will be invited to complete a travel survey on attending their screening appointment. The survey will gather detailed information on how participants travelled to the screening site, including mode of transport, journey duration, travel cost and whether they travelled alone. Participants will also be asked to provide their home postcode and starting location (eg, work or home), to enable estimation of travel distance and calculation of the study’s associated carbon footprint. The survey will further explore any difficulties encountered in attending the appointment, whether time had to be taken off work, and if the participant had previously attended a breast screening appointment. Additional demographic information will be collected, including GP practice, age group, ethnicity and whether English is their first language.

At the end of the travel survey, all women in the intervention arm will be asked whether they would be willing to take part in a follow-up interview for the qualitative component of the study. Those who express an interest will have the opportunity to provide their contact details within the survey for the research team to follow-up.

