## Introduction

 Breast cancer is the most commonly diagnosed cancer among women in the UK and in Yorkshire alone around 4300 women are diagnosed with breast cancer each year.^1^ Survival is closely linked to stage at diagnosis: 5-year survival for women diagnosed at Stage I is 97.9%; but falls sharply to 26% for those diagnosed at Stage IV.^2^ The National Health Service (NHS) breast screening programme was introduced to promote earlier detection, thereby improving survival outcomes.^3^ All women aged 50–70 years old are invited for breast screening every 3 years, yet uptake remains suboptimal. Yorkshire is a large region in northern England, comprising urban and rural areas with a diverse population. In Yorkshire, only 71.4% of eligible women attended their most recent screening appointment, with significant variation across the region.^4^ National data indicate that on average, 8.4 breast cancers are detected per 1000 women screened.^5^ Based on this rate, approximately 197 000 women did not attend screening in Yorkshire over a 3-year period, representing an estimated 1655 potentially detectable cases of breast cancer that may have been diagnosed at an earlier stage.^4 5^ Public Health England identifies 70% attendance as an acceptable threshold, but 80% as achievable.^6^ While Yorkshire marginally exceeds the acceptable level, it falls short of the achievable benchmark, with notable disparities in screening uptake across the region. Addressing barriers to participation is therefore a public health priority, particularly in areas of high deprivation and poor access to services. Improving uptake has the potential to significantly impact early detection and survival outcomes across the region.

Non-attendance at breast screening appointments is influenced by a range of factors, including a perceived lack of personal risk, cultural and religious beliefs, previous negative experiences, language barriers, embarrassment and practical difficulties in accessing the screening site.^7^,^9^ One of the most commonly reported barriers is limited access to screening facilities—either directly (eg, due to transport costs) or indirectly (eg, competing time commitments). Several studies have found that women who live further away from breast screening sites are significantly less likely to attend.^10 11^

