### Study aims and objectives

This feasibility trial is a necessary first step to evaluate the practicality of trial procedures, the fidelity of intervention delivery and to provide preliminary signals of effectiveness, estimate cost effectiveness and generate data to inform sample size calculations for a future definitive phase III randomised controlled trial.

The primary aim of this study is to assess feasibility across key domains:

Recruitment of GP practices.Implementation of the intervention.Data collection processes.Acceptability of the intervention.

In addition, the study will:

Provide an initial indication of efficacy.Generate preliminary cost-effectiveness data.Inform the design and sample size calculations for a potential definitive phase III randomised controlled trial.

Screening attendance data will be obtained from the NHS Breast Screening Service (NHS BSS) and this will be linked via NHS England through the Data Access Request Service (DARS) to deprivation and ethnicity data.

Travel surveys will be administered to participants in both the intervention and control arms to explore how women travel to screening appointments. To further assess the acceptability of the intervention, a subset of women from the intervention group—as well as representatives from the transport provider—will be invited to participate in qualitative interviews. These interviews will explore experiences of the transport offer, barriers or facilitators to use and perceptions of acceptability.

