### Randomisation

GP practices will be randomised 1:1 to the intervention arm or control arm with variable block sizes, stratified by area deprivation. Randomisation will be completed via the REDCap Cloud (RCC) online system provided by the Hull Health Trials Unit (HHTU).

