### Secondary outcomes

The secondary outcomes are the intended outcomes for the definitive trial, and the data that will help inform sample size calculations for the phase III trial.

Screening uptake rates: percentage attendance at screening appointments. This will explore a potential signal of efficacy by comparing uptake between the transport intervention arm and the control arm. To provide context, these rates will be benchmarked against historical screening uptake from the previous 3 years for the included GP practices.Transport intervention uptake rates.Cost-effectiveness: reporting estimates of cost-effectiveness of the transport intervention.

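### The ICC and effect size from eight practices are the only inputs named for sizing the definitive trial, and both will be too imprecise to serve as planning values

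*Protocol article*

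**What the plan says.** Sizing the later trial is a stated purpose of this one. Study aims and objectives says that it will "generate data to inform sample size calculations for a future definitive phase III randomised controlled trial". Secondary outcomes describes screening uptake and the other secondary measures as the outcomes intended for the definitive trial and as "the data that will help inform sample size calculations for the phase III trial". Data collection and statistical analysis names the inputs: "The intraclass coefficient calculated from this data and effect size of intended outcomes will be used to inform the sample size (power calculation").

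The base for those inputs is set out under Sample size: "The study sample size is estimated as 8000 women from eight GP practices". The number is justified as follows: "This is a pragmatic sample size based on the number of eligible women". The section then claims: "This sample size will allow for the reliable estimation of key feasibility figures and detection of signal of efficacy for the future full trial". No precision figure supports that claim. Under Randomisation, "GP practices will be randomised 1:1 to the intervention arm or control arm with variable block sizes, stratified by area deprivation", which gives four practices per arm if all eight are recruited. Table 1 puts recruitment in the red zone, as too few to supply sample-size data, only below six practices.

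The article mentions no minimum worthwhile difference and no other source for the ICC. Historical uptake appears under Secondary outcomes, but only for the included practices and only as a benchmark.

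**The concern.** An ICC is a between-practice variance, so its precision depends on the number of practices and hardly at all on the number of women. The effect estimate has the same limit, because it compares four practice rates with four others. If either estimate goes into a power calculation as a point value, its noise passes directly into the size of the definitive trial.

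The effect size is also a doubtful input in principle. According to the Introduction, the definitive trial is meant to inform commissioning. Its target should then be the smallest gain in uptake that would justify paying for transport, and a pilot difference does not estimate that.

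At stake is a definitive trial several-fold too small or too large. Nothing in this feasibility trial's allocation, data collection or progression criteria is affected.

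**Working it through.** The article states no alpha, power, ICC or target difference, so there is no power figure to reproduce. The one check available is that 8000 women / 8 practices = 1000 per practice.

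**Inputs from the article.** Eight practices, 1:1 allocation, m = 1000 women per practice, and baseline uptake p = 0.714 (Introduction: "In Yorkshire, only 71.4% of eligible women attended their most recent screening appointment").

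**Assumptions.** ICC ρ of 0.005, 0.01, 0.02 or 0.05; an illustrative gain of 5 points (71.4% to 76.4%); 90% power; two-sided 5% level; equal practice sizes.

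**Step 1: interval for the ICC.** Eight practices in two arms leave 8 − 2 = 6 between-practice degrees of freedom. The between-practice mean square has a 95% interval from 6/χ²(0.975; 6) = 0.415 to 6/χ²(0.025; 6) = 4.85 times its estimate, an 11.7-fold range. To carry this to the ICC, take F = 1 + mρ/(1 − ρ), divide by the upper and lower 2.5% points of the F distribution on 6 and 8 × 999 = 7992 degrees of freedom (2.410 and 0.2062), and convert back with ρ = (F − 1)/(F + m − 1). At ρ = 0.02, F = 21.41, with limits 8.88 and 103.8. These give ICCs of 7.88/1007.88 = 0.0078 and 102.8/1102.8 = 0.093.

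**Step 2: practices per arm in a definitive trial.** k = (1.96 + 1.2816)² × [p1(1 − p1) + p2(1 − p2)] × [1 + (m − 1)ρ] / (m d²). Here 10.507 × (0.2042 + 0.1803) / 0.05² = 1616 women per arm before the design effect. At ρ = 0.02 the design effect is 1 + 999 × 0.02 = 20.98, so k = 1616 × 20.98 / 1000 = 33.9. The two ICC limits give 14 and 152.

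**Step 3: effect estimate from four against four.** SE = √(2 × p(1 − p) × [1 + (m − 1)ρ] / 4000). At ρ = 0.02, SE = √(2 × 0.2042 × 20.98 / 4000) = 0.0463. If the true gain is 5 points, P(estimate ≤ 0) = Φ(−0.05/SE). By symmetry, P(estimate ≥ 10 points) is the same.

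| ICC | 95% CI from 8 practices | Upper/lower | Practices per arm: at the estimate (over the CI) | SE of difference, points | P(≤ 0), and equally P(≥ 10 points) |
|---|---|---|---|---|---|
| 0.005 | 0.0015–0.027 | 18 | 10 (4–46) | 2.5 | 2% |
| 0.01 | 0.0036–0.050 | 14 | 18 (7–83) | 3.3 | 7% |
| 0.02 | 0.0078–0.093 | 12 | 34 (14–152) | 4.6 | 14% |
| 0.05 | 0.021–0.206 | 10 | 82 (35–334) | 7.2 | 24% |

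Practice counts are rounded to the nearest whole number and carry no small-sample correction.

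**Step 4: what an inflated estimate would do.** Planning on 10 points (71.4% to 81.4%) needs 10.507 × (0.2042 + 0.1514) / 0.10² = 374 women per arm before the design effect. That is 374/1616 = 23% of the size needed for 5 points. At ρ = 0.02 it means about 8 practices per arm in place of 34.

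**Step 5: what wider routine data would give.** The number of practices that the screening service covers is not in the documents, so 30, 50 and 100 are assumed. By the Step 1 method, with K − 1 degrees of freedom, an ICC of 0.01 has an interval of 0.0060–0.0187, 0.0067–0.0160 or 0.0075–0.0138. The upper-to-lower ratios are 3.1, 2.4 and 1.8, against 14 from the eight trial practices.

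**The case against.** The strongest reply is that the article says the two estimates will inform the calculation. A reader might infer that the definitive trial will be powered on the observed point values alone and is therefore bound to be mis-sized. The text does not say that. It does not rule out using intervals or adding other inputs, it describes the efficacy output as preliminary, and it plans a decision model and a value-of-information analysis that could feed into the next design. Reporting of intervals is commonly left to an analysis plan, and the final target difference belongs in the definitive trial's own protocol. All of this stands. The point is limited to the fact that the article names these two inputs and no others, while calling the sample adequate for reliable estimation.

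It is also fair to say that the effect-size result depends heavily on the assumed ICC. At 0.005 a misleading estimate is uncommon (2% in each direction), and at 0.05 it is not (24%). The ICC result does not depend on the assumption in this way: the interval is at least 10-fold at every value tried.

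A reader might further infer that the screening service can supply uptake for every practice on its rota. The article shows only that the service provided internal data on eligible women, that invitations follow a 3-yearly practice rota, and that historical uptake is planned for the included practices. Wider availability is likely but not stated. A crude ICC across all practices would also include differences between deprivation levels, which a stratified trial removes. The fix allows for both.

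**Conclusion.** The concern holds in a limited form. The ICC and effect size from eight practices will be too imprecise to use as planning point values, and the article names nothing else for the purpose. The ICC interval spans 10- to 18-fold for ICCs of 0.005 to 0.05, and the implied size of an illustrative definitive trial varies roughly 10-fold across it. The effect estimate has a standard error of 2.5 to 7.2 points over the same ICCs.

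These figures rest on assumed ICCs, 1000 women in every practice, and six degrees of freedom. Allowing for deprivation strata, or recruiting only six or seven practices, would leave fewer degrees of freedom. The 5-point gain and 90% power are illustrative.

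This is a worthwhile low-cost improvement, not a condition for the trial to proceed. Sizing the later trial is listed in addition to the primary feasibility aim, and any harm would arise in a later protocol, where it can still be prevented.

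**What to change.** Replace the sentence under Data collection and statistical analysis with wording to this effect:

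- The definitive trial will be sized for a pre-specified minimum worthwhile difference in uptake, agreed with commissioners and informed by the economic model, and not for the difference observed here.
- The planning ICC will be estimated from previous-round counts of women invited and women attending, by practice, across as many practices as the screening service can supply. It will be estimated within deprivation strata to match the stratified design.
- This trial's ICC and effect will be reported with 95% confidence intervals as a check, and the definitive sample size will be shown over the ICC range.

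The cost is the rewording plus one aggregate extract, wider than the historical uptake already planned for the included practices. Recruitment, randomisation and the intervention are unchanged, and the extract can still be requested now that recruitment has opened. The screening service must confirm that the data are available and for how many practices. One service may not represent all later sites, so the sensitivity range should stay even if the extract is large.

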### Qualitative component

To explore women’s experiences and perceptions of the intervention, qualitative interviews will be conducted. In line with sample size recommendations for qualitative studies,^21^ we propose to interview approximately 30 women in the intervention arm. We will interview both women who attended and those who did not attend their screening appointments. Those who attended their screening appointments will be recruited through the final question on the travel survey. Women who did not attend their appointment (approximately 10) will be identified and contacted by HEY BSS.

The research team will recruit drivers (approximately 10) and transport provider managers to interview them about their views on the acceptability of the intervention.

The research team will send the volunteer participants an invitation letter, relevant participant information sheet detailing the purpose of the interview and what their participation would involve and a consent form. All the participants will complete a consent form before starting an interview. A copy of the study consent form is provided as online supplemental material (see separate uploaded document).

Interview recordings will be transcribed verbatim and analysed using thematic analysis.^22^ This would involve a three-stage process of identifying, analysing and interpreting themes (patterns of meanings) within the data. After data familiarisation, descriptive codes will be generated using words which describe participants’ views. These descriptive codes will be explored iteratively for patterns, similarities and differences, to develop themes. The themes will be reviewed in line with the research objectives and labelled accordingly. NVivo V.12 software (a qualitative data management software) will be used to manage the data analysis process. To ensure rigour, credibility and trustworthiness, data will be analysed by two researchers and conflicts resolved through discussion. A third researcher will be asked to mediate any unresolved conflict when necessary. Memos will also be kept to maintain an audit trail of the data analysis process. The theoretical framework of acceptability^23^ will provide a conceptual framework to understand the interview findings.

### Health economics

An economic evaluation will be conducted alongside the DOORSTEP feasibility trial. This will be conducted in two parts. Initially, a cost-effectiveness analysis will be conducted based on primary data collected within the trial. In addition, an economic model will be developed to explore the potential impact of the intervention on breast cancer detection and outcomes. Indicative estimates of cost-effectiveness will be generated. However, the key aim for the economic analysis in this feasibility study is to determine the plausibility of conducting an economic evaluation alongside a full trial, and to identify data gaps which would need to be addressed to facilitate this.

A decision analytical model will be developed in consultation with clinical experts, patient representatives and BSS, to facilitate exploration of the potential impact of the intervention on breast cancer detection and outcomes. The model will be generated using best practice methods, with the model structure, health states and parameter values being derived from the published literature, data from the DOORSTEP trial and where necessary, expert clinical opinion.^24^ A cost-utility analysis will be conducted based on the model outputs, following the National Institute for Health and Care Excellence (NICE) reference case for health technology appraisals.^25^ The outcome measure used in the model will be quality adjusted life years (QALYs) gained resulting from any increase in cancer detection as a result of screening. Results will be presented as expected incremental cost-effectiveness ratio which will be compared with the NICE cost-effectiveness threshold of £20 000–30 000 per QALY gained, and cost-effectiveness acceptability curves to demonstrate the probability of cost-effectiveness.^26^ Deterministic (one-way and scenario) and probabilistic (using Monte Carlo simulations) sensitivity analyses will be conducted to determine the impact of parameter value changes on estimates of cost-effectiveness and to establish the level of uncertainty surrounding the modelling results. A value of information analysis will also be conducted to estimate the value of conducting further research.^27^

The equity impact of the provision of free door-to-door transport for breast cancer screening will also be explored, for example, using distributional analysis or equity informative cost-effectiveness analysis (depending on data available), to identify potential distributional impacts on costs and benefits by measures of deprivation.^28^ This will be informed by area level deprivation data in relation to the location of the GP practice, along with data collected by the NHS BSS and NHS England.

### Outcome measures

This study is a feasibility trial with primary outcome measures designed to assess the feasibility of conducting a future definitive RCT. The primary and secondary feasibility outcomes are summarised below.

### Primary outcomes

The primary feasibility outcomes are summarised in table 1 along with criteria that will be used as a guide for progression to a future definitive phase III trial and described here:

Number of GP practices that agreed to participate and were randomised ahead of the scheduled breast screening invitation window.Percentage of women invited from GP practices located in the 10% most deprived areas.Percentage of intervention invites sent out by the BSS to all women during the scheduled breast screening invitation window.Percentage of women who requested transport who were transported to and from their appointment by the service.Acceptability of the intervention to the women and the service providers.Completion and transfer of the screening and transport service data when required for analysis.

**Table 1 T1:** Primary outcomes to assess feasibility and progression criteria

Feasibility outcomes	Outcome measure	Green	Amber	Red
Recruitment and randomisation of GP practices	Number of GP practices that agreed to participate and were randomised ahead of the scheduled breast screening invitation window.	8 (planned number of practices)	6–7 (numbers may still be achieved if invitations sent during part of the period, or less practices with more women)	<6 (insufficient number of practices/women included to provide data for sample size and feasibility estimates)
	Percentage of women invited from GP practices located in the 10% most deprived areas.	30%	15–30%	<15%
Fidelity of the transport intervention	Percentage of intervention invites sent out by the BSS to all women during the scheduled breast screening intervention window.	100% (all four intervention sites)	75%	<75%
Fulfilment of requests for the transport intervention	Percentage of women who requested transport who were transported to and from their appointment by the service.	100%	50–99% (explore reasons such as too many appts same date/time)	<50% (not viable to increase or change transport service to meet the demand)
Acceptability of the intervention to the women/service providers	Qualitative interviews.	Acceptable to all interviewed and no major barriers identified.	Acceptable with some modifications	Not acceptable to the majority of people interviewed
Completion and transfer of screening and transport service data when required for analysis	Screening service attendance data.	Screening data provided for all women in both arms of the trial.	Partial data provided	Data has not been transferred
	Transport providers.	Transport service data provided for all trips in the intervention arm of the trial.	Partial data provided	Data has not been transferred

BSS, breast screening service; GP, general practitioner.

